### Secondary outcome measures

Secondary endpoints for this RCT include:

• length of ICU stay starting from application of study medication

• ICU and hospital mortality, 28-day mortality, 6-month mortality

• percentage of patients with 25(OH)D levels ≥ 30 ng/ml at day 7

• duration of mechanical ventilation including CPAP/mask ventilation starting from application of study medication

• need for a tracheostomy during ICU stay

• surrogate markers for cardiac function: need for vasopressor therapy during ICU stay, and duration of such need, NT-proBNP levels

• analysis of biochemical and endocrine variables relevant to calcium- and phosphorus metabolism; 1,25(OH)D and PTH at days 0,3,7, 28 and month 6

• C-Reactive Protein and procalcitonin levels

• clinical parameters at 6 months (falls, Timed Up & Go – test, hand grip strength, lumbar and hip BMD, Quality of life and performance status, number of hospitalizations, number of respiratory tract infections)

• serum cathelicidin levels at day 0 and 7 are planned to be analyzed from frozen samples and will be reported separately

### Data collected at study entry

At baseline, data on demographic and clinical characteristics of the patients are obtained. Simplified Acute Physiology Score (SAPS II), presence of comorbidities, medical history, admission diagnosis by category and relevant medication are registered.

The following categories for diagnosis at admission and concomitant diagnoses are predefined:

• Surgical ICU admissions:

• trauma, cardiac surgery, vascular surgery, thoracic surgery, brain surgery, transplantation, other surgical reasons

• Medical or neurological ICU admissions:

• cardiovascular, respiratory, hematological/oncological, sepsis/infectious, gastrointestinal/hepatic, renal, metabolic, neurological, other non-surgical reasons

In addition, we record the need for and the number of days of hemodynamic support and mechanical ventilation including noninvasive ventilation and tracheostomy as well as the quantity and formula of enteral/parenteral nutrition given. Information on insulin requirements and use of antibiotics are registered on day 0, 2 and 6.

### Blood and urinary samples

Venous blood samples are taken upon ICU admission and in the morning on days 0,3,7,28 if feasible. Analyses include routine serum chemistry, hematology, markers of inflammation and parameters of calcium and vitamin D metabolism. Additional measurements of markers of metabolism and inflammation as well as other endocrine parameters are planned on stored samples that are frozen and stored at −70°C.

### 25(OH)D assay

25(OH)D serum levels are measured by ELISA (Immunodiagnostic Systems, Boldon, UK).

### Reminder calls and follow-up procedures

All patients who leave the hospital are contacted by telephone on a monthly basis to check for compliance with the monthly intake of the study drug (5 times) and vital status.The long-term follow-up appointment at 6 and 24 months is performed in two ways, dependent on the patient’s mobility and preference:

• Variant A (estimated 80%): Follow-up visit by telephone

• Variant B (estimated 20%): Visit at the clinic, including additional:

• Blood and urinary testing (similar to that on days 0,3,7,28)

• Timed Up & Go – Test (in seconds)

• Hand grip strength (in mmHg)

• Dual X-ray absorptiometry (DXA) with bone mineral density (at the hip and the lumbar spine) and body composition

The following data set is collected in all patients:

• Compliance with intake of study drug (number of maintenance doses)

• Additional vitamin D intake

• Falls and fractures since study inclusion (number)

• Respiratory tract infections (number and use of antibiotics)

• Hospitalizations (number and cause)

• Performance status (Eastern Cooperative Oncology Group (ECOG) Score)

• Quality of life

### Data management

Data is manually transferred from source files into paper-based primary CRFs identified by ascending patient numbers specific to respective ICUs. Data are then checked for accuracy and transferred to an electronic CRF by the clinical research assistance team. Extensive verification checks are performed by a study monitor. Vital status at 6 months is recorded for all patients.

### Safety assessment

Blinded safety assessment for 28-day mortality is planned after 100 and 240 patients. In case there is a safety concern, a standby data safety monitoring board meeting is planned.

### Sample size calculation

The sample size was calculated to detect a difference in mean length of hospital stay of 2 days with 80% power and a significance level of 5%. Using the Mann–Whitney U-Test for sample size calculation, a group size of 234 is needed to show a reduction of 2 days (equivalent to 14%) of the primary study outcome based on a mean hospital stay of 14 days and standard deviation of 7 days for the control group. To consider drop-outs of the study, a sample of 480 patients (240 per arm) was considered appropriate.

### Statistical analyses

The primary analysis for comparing length of hospital stay between the two groups will be made using the Mann–Whitney U-test. For secondary endpoints, differences between the two groups will be evaluated with the t test or Mann–Whitney U-test for continuous variables as appropriate and for categorical variables with the chi-square or Fisher Exact test. Survival endpoints will be displayed in Kaplan-Meier plots and compared by the log rank test. Furthermore, linear and logistic regression models will be applied to adjust for age, disease severity and 25(OH)D.

A CONSORT diagram will be reported (Figure
2). Analyses will be performed both on intention to treat and per protocol population with the intention-to-treat population as the primary. To assess compliance with the study protocol, the number of study drug maintenance doses will be reported.

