## Methods/design

### Study design

The VITdAL@ICU trial is an investigator-initiated, non-commercial, double-blind, placebo-controlled randomized clinical trial. This study compares high-dose oral cholecalciferol (vitamin D3) versus placebo treatment in a mixed population of 480 critically ill patients with low 25(OH)D levels at study enrollment (≤ 20ng/ml). Following an initial loading dose of 540,000 IU of vitamin D3, patients receive 90,000 IU of vitamin D3 on a monthly basis for 5 months resulting in a total treatment/observation period of 6 months. The VITdAL@ICU study is conducted at the Medical University of Graz, Austria, a tertiary care university hospital with a catchment area covering the Southeast of Austria (population approximately 1.5 million). It recruits patients from five ICUs: medical (15 beds), neurological (8 beds), cardiothoracic surgery (13 beds) and two mixed surgery units (12 and 10 beds, respectively).

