### Randomization

Patients at each of the five ICUs are randomly assigned to one of the two treatment study groups, “Vitamin D” or “Placebo”, in a 1:1 ratio, using the web-based randomization tool “Randomizer for Clinical Trials” (
http://www.randomizer.at). Block randomization is used with patients stratified according to ICU and gender.

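### ICU and gender are used to stratify randomisation but appear in no stated analysis: if they predict hospital stay, the primary test is valid but conservative and forgoes roughly 1 to 5 points of power

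*Protocol article*

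**What the plan says.** Three sections of the protocol article bear on this.

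- **Randomization:** allocation is "in a 1:1 ratio, using the web-based randomization tool" named there, and "Block randomization is used with patients stratified according to ICU and gender". The block size is not given.
- **Study design:** the ICU factor has five levels of different specialty: "It recruits patients from five ICUs: medical (15 beds), neurological (8 beds), cardiothoracic surgery (13 beds) and two mixed surgery units" (12 and 10 beds). With two genders this makes 5 × 2 = 10 strata.
- **Statistical analyses:** "The primary analysis for comparing length of hospital stay between the two groups will be made using the" Mann–Whitney U-test. No stratification is named. Further on, "linear and logistic regression models will be applied to adjust for age, disease severity and 25(OH)D". ICU and gender are not in that list.

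The Sample size calculation section uses the same unstratified test and aims to "detect a difference in mean length of hospital stay of 2 days with 80% power and a significance level of 5"%. It takes a mean of 14 days and an SD of 7 days for the control group and arrives at 234 per arm, raised to 240 for drop-outs.

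**The concern.** Blocks within strata force the arms to be nearly equal inside every ICU-by-gender cell. Differences in stay between, say, the neurological and the cardiothoracic unit then contribute almost nothing to the difference between arms. An unstratified rank test does not know this. Its null variance still includes the between-stratum spread, so the standard error is too large and the p-value too high whenever the strata are prognostic.

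What is at stake is efficiency, not validity. The design has little slack: 2 × 234 = 468 evaluable patients are needed and 480 are planned, an allowance of 12/480 = 2.5%. A few points of power that need no further data are worth having.

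**Working it through.** **1. The plan's own figure.** A reduction of 14% of 14 days is 1.96 days, and 1.96/7 gives d = 0.28. A two-sample t-test at two-sided 5% (sidedness is not stated, so two-sided is assumed) and 80% power needs 201.2, so 202 per arm. Dividing by 0.864, the minimum asymptotic relative efficiency of the Mann–Whitney test, gives 202/0.864 = 233.8, so 234. This matches. The calculation makes no use of the strata.

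**2. Size and power under stratified allocation.** Let R² be the share of rank variance explained by the 10 strata. The article gives no value, so a range is assumed. Set the unstratified test to 80% power at R² = 0, so that the expected test statistic is 1.960 + 0.842 = 2.802. Stratified blocks shrink the true variance of the contrast by the factor 1 − R², while the unstratified test keeps the full variance. Hence:

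- size, unstratified = 2Φ(−1.960/√(1 − R²))
- power, unstratified = Φ(0.842/√(1 − R²))
- power, stratified = Φ(2.802/√(1 − R²) − 1.960)

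For R² = 10%, √0.90 = 0.9487. Size = 2Φ(−2.066) = 3.9%. Unstratified power = Φ(0.887) = 81.3%. Stratified power = Φ(2.953 − 1.960) = Φ(0.993) = 84.0%.

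| Assumed R² | Size, unstratified | Power, unstratified | Power, stratified | Gap (points) |
|---|---|---|---|---|
| 0% | 5.0% | 80.0% | 80.0% | 0 |
| 5% | 4.4% | 80.6% | 82.0% | 1.4 |
| 10% | 3.9% | 81.3% | 84.0% | 2.7 |
| 15% | 3.4% | 81.9% | 86.0% | 4.0 |
| 20% | 2.8% | 82.7% | 87.9% | 5.3 |

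Gaps are taken before rounding.

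**3. Check by simulation.** Assumptions: 480 patients, ICU shares proportional to beds, a 60/40 gender split, blocks of 4, a normal outcome with *total* SD 7, 6,000 null trials and 3,000 trials per power figure. MW is Mann–Whitney, VE is van Elteren.

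| Assumed R² | Size MW / VE | Power, 2-day shift, MW / VE | Power, 1.75-day shift, MW / VE |
|---|---|---|---|
| 0% | 4.6% / 4.4% | 86.1% / 85.7% | 75.0% / 74.4% |
| 5% | 4.0% / 4.8% | 87.2% / 87.5% | 77.2% / 78.1% |
| 10% | 4.3% / 5.4% | 87.5% / 89.1% | 76.9% / 80.0% |
| 20% | 3.1% / 5.0% | 88.4% / 92.3% | 77.9% / 83.8% |

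Power at 2 days exceeds 80% because 234 was obtained with the pessimistic efficiency of 0.864, whereas the simulated outcome is normal. The pattern agrees with step 2. MW size drifts below 5% as R² rises while VE size stays near it. The power gap at R² = 20% is 3.9 points for a 2-day shift and 5.9 points for a 1.75-day shift. At R² = 0, VE costs 0.4 to 0.7 points. MW power does not decline as R² rises.

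**The case against.** The strongest reply is that nothing is broken. The type I error is not inflated, and the sample size was computed for the very test that is planned, so design and analysis agree. The regression models are supplementary, and a separate statistical analysis plan, not shown, may deal with the strata. The benefit also rests on an R² that the article does not give and could be near zero.

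Most of this stands and limits the point to a conditional gain in efficiency. The appeal to a separate plan carries less weight, because the article itself names the primary test and lists the covariates. A plan that stratified the test would be changing what the article states.

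Three stronger readings are tempting, and the documents support none of them.

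- *The trial falls short of 80% power.* A reader might infer this from a simulation that adds stratum variance on top of a within-stratum SD of 7: Mann–Whitney power then appears to fall steadily. But the SD of 7 days is stated for the control group as a whole, so it already contains the spread between ICUs. With total SD held at 7, Mann–Whitney power stays level or rises slightly.
- *Stratifying lifts 80% to 84%, 86% or 88%.* These stratified figures (R² of 10%, 15% and 20%) need the right comparator. Under the same allocation the unstratified test itself reaches about 81%, 82% and 83%.
- *Stratifying is worth 53 to 120 extra patients* (480/0.90 = 533 to 480/0.80 = 600). Most of that precision is already delivered by the stratified allocation. The stratified analysis mainly corrects the standard error.

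**Conclusion.** The mismatch is a plain fact of the text: two stratification factors, and no stated analysis that uses either. Its consequence is conditional. Five ICUs of different specialty make some prognostic value plausible, and in that case the planned test is conservative and gives up roughly 1 to 5 points of power for R² between 5% and 20%. These figures rest on the assumed R², a two-sided 5% level and a normal approximation supported by simulation. The point is a worthwhile, nearly free improvement, not an error that endangers the trial's conclusions.

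**What to change.** By documented amendment, made before unblinding:

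1. Make the primary test a van Elteren test stratified by ICU and gender.
2. Report a stratified Hodges–Lehmann shift in days with its 95% CI.
3. Keep the unstratified Mann–Whitney test as a sensitivity analysis.
4. Add ICU and gender to the adjusted linear and logistic models, which costs 4 + 1 = 5 further parameters.

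The strata are large enough. The average is 480/10 = 48 patients. With recruitment proportional to beds and 40% in the smaller gender group (both assumptions), the smallest stratum would hold about 480 × 8/58 × 0.40 ≈ 26.

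No new data are needed, since both factors are known at randomisation. The statistical price is at most about 1 point of power if the strata turn out unrelated to stay. The administrative price is a dated amendment with its rationale: the Discussion reports that the trial is running and that the safety looks at 100 and 240 patients are done, so the record should show that the change was made without knowledge of outcome by arm.

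### The primary test of hospital stay leaves out baseline age and severity already collected; adjusting it would probably gain some power at little cost

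*Protocol article*

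**What the plan says.** The Statistical analyses section names the deciding comparison: "The primary analysis for comparing length of hospital stay between the two groups will be made using the" Mann–Whitney U-test. No covariate or stratum enters it. After the tests for the secondary endpoints, the section adds: "Furthermore, linear and logistic regression models will be applied to adjust for age, disease severity and 25(OH)D". It does not say which outcomes those models serve, on what scale stay would be modelled, or which variable measures disease severity.

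The baseline information exists. Under Data collected at study entry, "At baseline, data on demographic and clinical characteristics of the patients are obtained", and "Simplified Acute Physiology Score (SAPS II), presence of comorbidities, medical history, admission diagnosis by category and relevant medication are registered". Under Randomization, "Block randomization is used with patients stratified according to ICU and gender"; neither factor appears in the primary test. The Sample size calculation section used the Mann–Whitney test, so planned size and planned analysis agree.

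**The concern.** The trial recruits from medical, neurological, cardiothoracic and mixed surgical ICUs, so stay is likely to vary with the kind of patient as well as with treatment. Any part of that variation that baseline variables predict stays in the unadjusted comparison as noise. The investigators evidently regard age and severity as worth adjusting for, but only in supplementary models. Moving such covariates into the primary rank analysis would need no extra patients or data. At stake is some power for the primary endpoint, in a trial whose drop-out allowance is small: 480 enrolled against 2 × 234 = 468 needed, or 1 − 468/480 = 2.5%.

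**Working it through.** **Inputs.** From Sample size calculation: control mean 14 days, SD 7 days, reduction of 2 days (also given as 14%), 80% power, 5% significance level, 234 per arm, 240 per arm with drop-outs. Sidedness is not stated; two-sided is assumed. The share R² of the variance of ranked stay explained by baseline covariates is not in the article; 0.05, 0.10 and 0.20 are assumed.

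**Step 1: reproduce the plan's own figure.** For a t-test, n per arm = 2 × (1.960 + 0.842)² × SD² / δ². With δ = 14% of 14 = 1.96 days, this is 769.2 / 3.842 = 200.2, so 201. Dividing by 0.864, the minimum asymptotic efficiency of the Mann–Whitney test relative to the t-test, gives 201 / 0.864 = 232.6, so 233, one short of the stated 234. With exactly 2 days the same route gives 193 / 0.864 = 223.4, so 224. The stated size is sound and, for 2 days, slightly conservative.

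**Step 2: effect of adjustment, normal approximation.** Take the plan's 80% at 234 per arm as given. At 240 per arm the expected z is (1.960 + 0.842) × √(240/234) = 2.837, and power = Φ(2.837 − 1.960) = 81.0%. Adjustment multiplies the residual variance by (1 − R²), so power = Φ(2.837/√(1 − R²) − 1.960):

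| R² (assumed) | z | Power at 240 per arm | Gain (points) | n per arm for 80%: 234 × (1 − R²) |
|---|---|---|---|---|
| 0 | 2.837 | 81.0% | – | 234 |
| 0.05 | 2.911 | 82.9% | 1.9 | 223 |
| 0.10 | 2.991 | 84.9% | 3.9 | 211 |
| 0.20 | 3.172 | 88.7% | 7.7 | 188 |

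**Step 3: simulation.** The Mann–Whitney test was compared with rank ANCOVA, with control mean 14 and SD 7:

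| Stay | R² | Mann–Whitney | Rank ANCOVA | Gain (points) |
|---|---|---|---|---|
| Lognormal, 240 per arm, 1.7-day shift, 1,500 runs | 0.05 | 89.5% | 90.5% | 1.0 |
| | 0.10 | 90.5% | 92.6% | 2.1 |
| | 0.20 | 90.7% | 95.6% | 4.9 |
| Lognormal, 234 per arm, mean 14 to 12 (proportional), 4,000 runs | 0.10 | 93.9% | 95.4% | 1.5 |
| | 0.20 | 92.7% | 96.4% | 3.7 |
| Normal, 234 per arm, 2-day shift, 4,000 runs | 0.10 | 85.8% | 89.3% | 3.5 |
| | 0.20 | 85.9% | 93.0% | 7.1 |

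In the first lognormal setting, rejection under the null was 4.3% to 5.7% for both tests. A single rate near 90% from 1,500 runs has a standard error of √(0.9 × 0.1 / 1,500) = 0.8 points, so the 1-point gain at R² = 0.05 is barely resolved. With skewed stay the rank test already has about 90% power or more, which leaves less to gain than Step 2 suggests.

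**Step 4: what these calculations leave out.** Under Primary outcome measures, stay ends at discharge or at death. Severity may lengthen stay in survivors and shorten it in patients who die early. A single monotone severity term could then explain little of ranked stay, and R² could be close to zero. None of the simulations includes deaths.

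**The case against.** The strongest reply is that nothing here is wrong: a valid, prespecified test matches the test used for the sample size. That stands, and it limits the point to efficiency. It is also fair that the article gives no R², that the skewed-data gains are smaller than those from the normal approximation, and that the way stay ends may weaken SAPS II as a predictor. All three stand and set the range.

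A reader might infer more than the text supports:

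- That the linear model is one of raw days, and so at the mercy of a few very long stays. The article gives neither its outcome nor its scale; a log scale is not excluded, and such detail may sit in an analysis plan that is not shown.
- That SAPS II is already named for adjustment. The phrase is "linear and logistic regression models will be applied to adjust for age, disease severity and 25(OH)D"; SAPS II is the likely measure of severity but is not named there.
- That nothing settles a disagreement between adjusted and unadjusted results. The section does: the Mann–Whitney test is primary and the models are additional.

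It would also be inconsistent to blame noise on the mix of units and then adjust only for age, SAPS II and 25(OH)D. An adjusted model meant to remove that noise should contain ICU.

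**Conclusion.** The point holds as a missed gain in efficiency. The primary comparison uses no baseline information, although age and SAPS II are available and age and severity are already considered worth adjusting for. At 240 per arm the normal approximation puts the gain at about 2, 4 or 8 percentage points for R² of 0.05, 0.10 or 0.20. With skewed stay it is about 1 to 5 points from a higher starting power. Both ranges rest on assumed R² values, a two-sided 5% test and no modelling of deaths; a gain near zero is possible. It does not follow that the trial is underpowered, that 234 per arm is wrong or that the Mann–Whitney result would be unreliable.

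**What to change.** Before unblinding, prespecify as primary a covariate-adjusted rank or ordinal analysis of stay: rank ANCOVA or a proportional-odds model, with arm, age, SAPS II and ICU. Gender may be added as the other stratification factor. If 25(OH)D is included, use only the pre-dose value. The Safety endpoints section also has it measured on days 3 and 7, and adjusting for a value that treatment has changed would remove part of the effect. Eligibility already restricts baseline 25(OH)D to 20 ng/ml or less, so it may add little.

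Keep the unadjusted Mann–Whitney test as the stated sensitivity analysis, and treat deaths identically in both.

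The cost is a few lines of text and no new data. The primary test becomes slightly harder to describe, a simple rule is needed for a missing SAPS II value, and the handling of deaths has to be written down.

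### Secondary blood markers with a day-0 sample are compared by unadjusted two-sample tests, and the stated adjustment set omits the marker's own day-0 value: valid, but less efficient than it need be

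*Protocol article*

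**What the plan says.** All references are to the protocol article.

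- **Tests.** Under Statistical analyses, for continuous secondary endpoints, "differences between the two groups will be evaluated with the t test or" the Mann–Whitney test, whichever suits the data. The section does not say whether the follow-up value or the change from day 0 is tested.
- **Adjustment.** The same section adds that "linear and logistic regression models will be applied to adjust for age, disease severity and 25(OH)D". It does not say to which endpoints this applies or when the 25(OH)D covariate is measured.
- **Markers.** Secondary outcome measures lists variables of calcium and phosphorus metabolism, with "1,25(OH)D and PTH at days 0,3,7, 28 and month 6", and also "C-Reactive Protein and procalcitonin levels", the latter without time points.
- **Sampling.** Blood and urinary samples states: "Venous blood samples are taken upon ICU admission and in the morning on days 0,3,7,28 if feasible". The analyses there include routine chemistry, inflammation markers and calcium and vitamin D parameters. Safety endpoints also gives serum calcium at days 0, 3 and 7, with day 28 and month 6 where available.
- **Strata.** Randomization is blocked and stratified by ICU (five units) and gender.

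**The concern.** A marker's day-0 value is often the best single predictor of its value a few days later. Where it is already scheduled, a comparison that ignores it carries between-patient variation that could have been removed. Any chance imbalance at day 0 also passes into the day-3 and day-7 comparison in proportion to r. The trial mixes medical, neurological and surgical ICU patients, so wide spread at day 0 is plausible, although the article gives no figure for it.

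Precision also matters because samples thin out. They are taken only where feasible. Reminder calls and follow-up procedures expects about 20% of patients at the clinic visit where later blood is drawn, so at month 6 at most about 0.20 × 480 = 96 patients, or 48 per arm, before deaths.

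At stake is efficiency on secondary endpoints. Bias and type I error are not in question.

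**Working it through.** **The plan's own figure.** The article gives no power, precision or correlation for the markers, so there is nothing to reproduce. Its group size of 234 belongs to length of hospital stay and plays no part here.

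**Inputs**
- From the article: 240 patients per arm; sampling at days 0, 3 and 7; five ICUs; gender as a stratum.
- Assumed: r, the correlation within arm between day-0 and follow-up values on the scale analysed, from 0.2 to 0.8; two-sided 5% level.

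**Formulas.** With n per arm and follow-up standard deviation σ, the variance of the between-arm difference is:
- follow-up value only: 2σ²/n, taken as 1;
- change from day 0 (equal spread at both times): 2(1 − r) relative to that;
- linear model with the day-0 value as covariate (ANCOVA): 1 − r² relative to that.

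ANCOVA against change is (1 − r²) / [2(1 − r)] = (1 + r)/2, which is at most 1. In large samples ANCOVA is therefore no less precise than either two-sample test.

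For an effect with 80% power unadjusted, the adjusted power is Φ[(1.96 + 0.84)/√(1 − r²) − 1.96].

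| Assumed r | ANCOVA 1 − r² | Fall in variance | Change 2(1 − r) | n per arm matching 240 unadjusted | Power (80% unadjusted) |
|---|---|---|---|---|---|
| 0.2 | 0.96 | 4% | 1.60 | 230 | 82% |
| 0.3 | 0.91 | 9% | 1.40 | 218 | 84% |
| 0.5 | 0.75 | 25% | 1.00 | 180 | 90% |
| 0.7 | 0.51 | 49% | 0.60 | 122 | 97.5% |
| 0.8 | 0.36 | 64% | 0.40 | 86 | 99.7% |

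Example: at r = 0.5, 1 − 0.25 = 0.75 and 240 × 0.75 = 180.

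**Change scores.** Up to r = 0.5 a test on changes is no better than ignoring day 0. Reading the plan as a test on changes therefore does not remove the point.

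**Mann–Whitney.** Its result is the same on raw or log values. If the logs are normal, its efficiency against the t test is 3/π = 0.955, so the table applies to it approximately.

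**Price of the covariates.** Four coefficients for five ICUs, one for gender and one for the day-0 value make six. At full sample that costs about 6/480 = 1.25% in variance. Without counting any gain from ICU and gender, adjustment is near break-even at r = 0.1 (1 − 0.01 = 0.99) and pays from r = 0.2 upwards.

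**The case against.** **Adjustment is already planned.** This stands in part. Covariate-adjusted regression is stated, so it would be wrong to say that the plan has only unadjusted tests. But its covariate list is explicit and leaves out both the marker's own day-0 value and the strata. Day-0 25(OH)D is a weak stand-in for, say, day-0 CRP, because entry requires a level of 20 ng/ml or less and so truncates its range. If a post-dose 25(OH)D were meant, the model would adjust for a consequence of treatment.

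**The day-0 value is not said to be discarded.** This stands. A reader might infer from the named tests that day-0 data are thrown away, but the text fixes the test and not the quantity tested.

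**A large loss of precision is not shown.** This also stands. A reader might take r of 0.5 or more for granted and conclude that much of the precision is lost. The article gives no correlation, r will differ between markers, and at r = 0.2 or 0.3 the gain is only 4% or 9%.

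**Not every marker has an explicit day-0 value.** NT-proBNP has no time points and is not named in the sampling section, so it is left out here. CRP and procalcitonin come in only through the general mention of inflammation markers. The text does not say that the day-0 sample precedes dosing. The main 25(OH)D endpoint, "percentage of patients with 25(OH)D levels ≥ 30 ng/ml at day 7", is a proportion and falls under other tests. Cathelicidin is to be reported separately.

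**The tests are valid, and a condensed article may leave covariates to an analysis plan.** Validity is granted. The article does, however, state both a method and an adjustment set, and the method it states can be improved at almost no cost.

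**Conclusion.** The point holds as an efficiency point on secondary endpoints. For PTH, 1,25(OH)D, calcium and phosphorus variables, CRP and procalcitonin, no stated analysis uses the marker's own day-0 value or the strata, although day-0 sampling is scheduled. Baseline adjustment would lower the variance by between 4% (r = 0.2) and 64% (r = 0.8), and by a quarter at r = 0.5. The omission can be read from the text. The size of the gain cannot, because it rests wholly on assumed correlations. The comparison with change scores further assumes equal spread at both times. The primary endpoint, length of hospital stay, has no day-0 value and is unaffected.

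**What to change.** 1. For each of these markers, make the between-group comparison at day 3 and at day 7 a linear model on the log value where the marker is skewed. Use the marker's own day-0 value (also logged), ICU and gender as covariates. Report the ratio of geometric means with its 95% confidence interval, or the adjusted mean difference for a marker left unlogged.
2. Keep the t or Mann–Whitney test as a sensitivity analysis, and say whether it is run on the follow-up value or on the change.
3. State that any 25(OH)D covariate is the day-0 value, and that a day-0 covariate must come from a sample drawn before the first dose.
4. Say how a missing day-0 sample is handled, since sampling is subject to feasibility.

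A mixed model that also takes in day 28 is optional. It needs explicit assumptions about samples missing through death or discharge, so it is not a cost-free addition. The separate models at days 3 and 7 use the same follow-up samples as the two-sample tests.

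The cost is analysis wording and a little programming. No sample, visit or patient is added.
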